## Abstract

**Background:**

Coronary heart disease (CHD) is a common cardiovascular disease accounting for 10–20% mortality by heart disease worldwide. The gold standard treatment to manage CHD is aspirin, which may prevent myocardial infarction and sudden death; however, long-term use of aspirin may increase its side effects. Currently, more and more clinicians are exploring different approaches to use the right combination of medicine to enhance the efficacy and reduce side effects. Salvianolate can significantly inhibit the aggregation and activation of platelets in patients with CHD; however, its optimum combination with western medicine is not established or supported by clinical trial results.

**Methods/design:**

This trial is a prospectively planned, open-labeled, parallel-grouped, single-centered clinical trial with aggregated pharmacodynamics-pharmacokinetics (PK-PD) data. All treatment courses will last for 10 days and blood sample will be acquired before administration on days 8, 9, and 10, and after administration at 5 min, 15 min, 30 min, 45 min, 1 h, 2 h, 4 h, 8 h, 12 h, and 24 h on day 10. This trial uses PK-PD modeling to provide a description of the concentration–effect relationship and an estimate of pharmacological potency of the medicine. The primary outcome will be changes in aspirin esterase and catechol-o-methyltransferase (COMT) activity at different blood concentrations to determine the PK-PD characteristics of the combination of salvianolate and aspirin, followed by analysis of the correlation between exposure level and pharmacodynamic index of the medicines.

**Discussion:**

This trial will aim to evaluate the relationship between changes in the pharmacokinetics and therapeutic effect index in the combined use of salvianolate and aspirin. It also discusses the possible mechanism of medicine combination in the treatment for CHD and provides an experimental basis for a clinically rational medicine combination.

**Trial registration:**

ClinicalTrials.gov, NCT03306550. Registered on 9 October 2017. ClinicalTrials.gov https://register.clinicaltrials.gov/prs/app/action/SelectProtocol?sid=S0007D8H&selectaction=Edit&uid=U0003QY8&ts=2&cx=oiuc9g

**Electronic supplementary material:**

The online version of this article (10.1186/s13063-018-2861-7) contains supplementary material, which is available to authorized users.

## Background

Nowadays, cardiovascular disease has become the most important disease affecting human health [1] ; the mortality of coronary heart disease (CHD) accounts for 10–20% of total mortality by heart disease worldwide. Guidelines for the diagnosis and treatment of CHD indicate that the main objective of drug therapy for CHD is to prevent myocardial infarction and sudden death and the first choice of treatment is aspirin. Aspirin can effectively inhibit platelet aggregation and prevent blood coagulation and thrombosis [2]. However, its long-term use can increase the risk of gastric mucosa injury, bleeding, hemolysis, and hematopoietic dysfunction [3]. Therefore, more and more clinicians are exploring different approaches to use the right combination of medicine to enhance efficacy and reduce side effects. However, the optimum combination of Chinese and western medicine is not established or supported by clinical trial results; it remains unclear whether the interaction between Chinese and western medicine leads to interactions in one or more stages of pharmacodynamics and whether the interactions are synergistic or antagonistic in nature. Moreover, it is challenging to determine the appropriate dosage and route of administration to achieve the maximum clinical efficacy of the combined application of Chinese and western medicine. These are all scientific questions that need to be studied.

### Aspirin

Aspirin is among the most commonly used drugs worldwide. Its widespread use is attributed to the high prevalence of ischemic heart disease and cerebrovascular accidents, along with its proven efficacy in preventing them. Clinical trials show that antiplatelet therapy with aspirin reduces the risk of myocardial infarction, stroke, and vascular death. Aspirin can prevent platelet aggregation because it leads to decreased thromboxane A2 (TXA2) through the inhibition of cyclooxygenase (COX) combined with removed acetyl [4, 5]. The whole process deacetylates by several kinds of esterase in digestive juice and blood after oral administration. Therefore, the curative effect of aspirin may rely on its deacetylation rate in the human body. Aspirin’s curative effect may decline if it hydrolyzes too rapidly in the digestive juice and blood [6].

### Salvianolate injection

Salvianolate injection is a listed injection composed mainly of magnesium lithospermate, which constitutes > 80%, and magnesium acetate homologs. Salvianolate regulates blood circulation, blood stasis, and pulse [7]. It is used for stable angina, a class I and II CHD with mild and moderate symptoms. Recently, a favorable clinical effect has been observed in the treatment of stable angina by injection of salvianolate combined with western medicine. It is widely used in combination with aspirin, isosorbide dinitrate, calcium antagonists, ACEI, and ARB. Many clinical findings show that the combination of salvianolate injection and routine western medicine for treatment of CHD has better clinical efficacy than only medication [8].

Salvianolate can significantly inhibit the aggregation and activation of platelets in patients with unstable angina pectoris, improve microcirculation, and prevent microthrombus formation [9, 10]. It prevents platelet aggregation by reducing the platelet aggregation rate, inhibiting p-selectin expression, and reducing matrix metalloproteinase-9 activity. In CHD patients treated with clopidogrel and aspirin, it can further inhibit the expression of platelet activation complexes membrane glycoprotein GP IIb/IIIa and CD62p [11]. In vitro experiments confirmed that salvianolate inhibits platelet activation and aggregation by inhibiting platelet PDE activity and directly antagonizing P2Y12 receptor [12].

### PK-PD

The PK-PD model comprises pharmacokinetics (PK) and pharmacodynamics (PD). This model has become increasingly important, especially in preclinical trials, to support drug discovery and determine optimal dosing strategies. The PK-PD model can provide a description of the concentration–effect relationship and an estimate of pharmacological potency of the drug. This methodology allows us to describe time dependence, discriminate inter-subject variability, and perform risk assessments at an individual level [13–15].

### Why is this study needed now?

Traditional Chinese medicine (TCM) has a long history of usage in China and is also widely used as alternative medicine worldwide [16, 17]. A survey shows that approximately 1.5 million adults in the United States use one or more kinds of herbal medicine while regularly taking prescription medications [18]. Meanwhile, several clinics in the UK use TCM. However, it is unclear whether drug–drug interaction (DDI) mechanisms between TCM and western medicine limit the application of TCM [19, 20]. Therefore, it is necessary to determine the DDI between TCM and western medicine. DDI can be divided into three groups: pharmacokinetics DDI; pharmacodynamics DDI; and in vitro DDI. Pharmacokinetics DDI generally involves the interaction of drugs in the process of absorption, distribution, metabolism, and excretion. TCM, which contains many bioactive ingredients, may engage in a synergistic or antagonistic interaction with other medicines. In this study, we focus on pharmacokinetics DDI between salvianolate and aspirin. Through the establishment of the PK-PD model, we aim to evaluate the relationship between the change of pharmacokinetics and therapeutic effect index in the combined use of salvianolate and aspirin. Finally, we discuss the possible mechanism of medicine combination in the treatment for CHD and provide an experimental basis for a clinically rational medicine combination.

## Objectives

The primary objective of this study is to determine the influence of salvianolate on the activity of aspirin esterase and that of aspirin on the activity of salvianolate metabolic enzyme.

The secondary objective is to determine the PK-PD characteristics of the salvianolate and aspirin combination and analyze the correlation between the exposure level and pharmacodynamic index of the medicines.

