## Proposed trial outcome measures

### Primary outcome

Change in aspirin esterase activity at different blood concentrations: biological analysis will be conducted by liquid chromatography tandem mass spectrometry (LC-MS/MS) to detect aspirin and salicylic aspirin and salicylic acid: CSA/C(ASA + SA). (Time frame: blood samples are acquired before aspirin administration on days 8 and 9. On day 10, blood samples are acquired before and after aspirin administration at 5 min, 15 min, 30 min, 45 min, 1 h, 2 h, 4 h, 8 h, 12 h, and 24 h.)Change in COMT activity at different blood concentrations: COMT activity is the main metabolic enzymes of SAB. A kit was used to detect COMT activity. (Time frame: blood samples are collected before injection on days 8 and 9. On day 10, blood samples are collected before and after injection at 5 min, 15 min, 30 min, 45 min, 1 h, 2 h, 4 h, 8 h, 12 h, and 24 h.)

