#### PD index

The results of the experimental, salvianolate, and aspirin arm will be compared by ANOVA analysis.

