## Discussion

A combination of salvianolate and aspirin may provide an effective and safe therapeutic option for patients with CHD; however, its DDI mechanism remains unclear. We investigate this inquiry by applying a PK-PD model. Research and clinical practice become intimately intertwined on the ground of PK-PD trials. We apply typical research instruments (e.g. randomization, control) to achieve the ultimate clinical objective, to reliably and empirically determine the best therapeutic choice for patients, and also meet the aims of innovative and timely research. This study establishes a PK-PD model to determine the PK-PD characteristics of the salvianolate and aspirin combination and analyze the correlation between exposure level and pharmacodynamic index of the medicines.

Metabolic enzymes play an important role in pharmacokinetics DDI. The main metabolic enzyme is CYP450, which is essential for the metabolism of many drugs. According to statistics, CYP450 isoforms are responsible for the oxidative metabolism of approximately 85% of the marketed drugs [22]. However, neither aspirin nor salvianolate injection has any relation with CYP450. Aspirin is hydrolyzed by several kinds of esterases [23–25] and the main active component of salvianolate, SAB, is metabolized by COMT. These enzymes might be the key point of pharmacokinetics DDI between aspirin and salvianolate injection. In this case, we plan to use ELISA to measure the activity of COMT and a formula containing aspirin and its metabolite, salicylic acid, to evaluate the activity of esterase. In summary, we analyze the pharmacokinetics DDI of salvianolate and aspirin through COMT and esterase, respectively, to determine the influence between the metabolic processes of each medicine. This research also explores the functional mechanism of the two medicines on the treatment of CHD. It is the trend to establish PK-PD based on functional mechanism. The function of salvianolate and aspirin is related to the inhibition of platelet aggregation and blood coagulation. Thus, we choose P-selection, PAC-1, and P2Y12 acceptor and PDE enzymes as efficacy indexes to explore their correlation with drug concentration.

Ultimately, this research, in its entirety, will provide an approach of filling the gap between science and practice, supplying evidence of DDI, and facilitating the use of medicine combination in the treatment of CHD.

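### The secondary objective relates exposure to both drugs to the PD indices, but the only concentration assay named is for aspirin and salicylic acid, and the analysis section gives only between-arm ANOVA

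*Protocol article*

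**What the plan says.** **Aim.** Under Objectives, the Protocol article sets as secondary objective to establish the PK-PD characteristics of the combination and to "analyze the correlation between the exposure level and pharmacodynamic index of the medicines". The plural covers both drugs. The section on why the study is needed says "In this study, we focus on pharmacokinetics DDI between salvianolate and aspirin". The abstract and the Discussion both announce a PK-PD model, and the abstract adds an analysis correlating exposure with effect.

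**Measurements.** Under Primary outcome, the first outcome uses "liquid chromatography tandem mass spectrometry (LC-MS/MS) to detect aspirin and salicylic aspirin and salicylic acid". The second is "Change in COMT activity at different blood concentrations", and its measurement is described so: "COMT activity is the main metabolic enzymes of SAB. A kit was used to detect COMT activity". Under Secondary outcome, three platelet markers are measured by flow cytometry and PDE by ELISA. Each is to be examined for the influence of aspirin or salvianolate over the drug's concentration curve.

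**Analysis.** In the statistical analysis section, esterase activity is compared across the three arms by ANOVA, and COMT activity by a column graph and ANOVA. For the PD index the whole text is: "The results of the experimental, salvianolate, and aspirin arm will be compared by ANOVA analysis".

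**The concern.** An exposure-response objective needs two things: a concentration for each drug whose exposure is to be related to effect, and an analysis in which that concentration appears. For salvianolate the article names neither. For aspirin it names the concentration but not the analysis.

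ANOVA on arm labels asks whether mean PD values differ between treatments. It cannot say whether a patient's platelet marker moves with that patient's drug level. If the trial is run and analysed as the article sets out, the salvianolate half of the secondary objective goes unanswered, and the aspirin half is left with usable data and no stated use for them. The listed measurements would also not show whether aspirin changes exposure to salvianolate, which bears on one direction of the PK interaction under study.

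**Working it through.** The article gives no figure to reproduce on this point, so the check is a comparison of sections and a count.

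**1. What each listed assay measures** (Primary outcome and Secondary outcome)

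| Outcome | Named method | A drug concentration? |
|---|---|---|
| Aspirin esterase activity | LC-MS/MS, aspirin and salicylic acid | Yes: aspirin and its metabolite |
| COMT activity | Kit | No: enzyme activity |
| P-selectin, PAC-1, P2Y12 | Flow cytometry | No: PD marker |
| PDE | ELISA | No: PD marker |

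Every listed outcome has a method, and none of the methods is stated to measure salvianolic acid B. Yet the Interventions section calls it the main ingredient of the injection, and the Discussion calls it the active component metabolised by COMT. The COMT outcome is itself framed against blood concentrations. In the salvianolate arm, no named assay supplies the concentration of the drug given.

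**2. Who is affected** (Study design, Randomization)

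- Per arm: 18 / 3 = 6.
- Receiving salvianolate: salvianolate arm + experimental arm = 6 + 6 = 12 of 18.
- Receiving aspirin: aspirin arm + experimental arm = 6 + 6 = 12 of 18.

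**3. Whether the sampling supports an exposure-response analysis**

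- PK times (Study design): pre-dose on days 8, 9 and 10, then ten post-dose times on day 10; 3 + 10 = 13.
- PD times (Secondary outcome): day 10 pre-dose, 15 min, 1 h, 2 h, 8 h and 24 h; 6 in all.
- Overlap: all 6 PD times are also PK times.
- Scheduled aspirin concentration-effect pairs per PD marker with the named assays: 12 x 6 = 72 (36 per arm).
- The 6 patients given salvianolate alone (6 x 6 = 36 PD time points) have no concentration of the drug they receive to pair with.
- With a salvianolic acid B assay, salvianolate would also have 12 x 6 = 72 pairs.

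The schedule is therefore adequate. The gap lies in the named analytes and in the analysis.

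**4. Why the analysis should be within patient**

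The 72 pairs are repeated measurements on 12 people, not 72 independent observations. Reducing each patient to one exposure and one effect value leaves n = 12. Assuming two-sided alpha 0.05 and 80% power (the article states neither), the Fisher z approximation gives a detectable correlation of tanh[(1.96 + 0.84) / sqrt(12 - 3)] = tanh(0.934) = 0.73. Only a strong correlation would be found that way. A within-patient analysis uses the change in concentration and effect over the six times, which is what the sampling was laid out to capture.

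**The case against.** The strongest reply is that this is a condensed article. Analyte lists, exposure metrics and model form commonly sit in a full protocol, bioanalytical plan or SAP, and none of these is shown. The text also presupposes salvianolate concentrations: the COMT outcome refers to blood levels, the PD outcomes refer to concentration curves for either drug, and the Study setting section sends samples to a pharmacokinetics laboratory. PK-PD modelling and arm comparisons can coexist.

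Much of that stands, and it rules out several stronger readings.

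- A reader might infer that the secondary objective is unattainable. The documents do not support this: aspirin and salicylic acid are measured at all six PD times, and an assay not named in an article is not proof that the drug goes unmeasured.
- A reader might infer that ANOVA is all that is planned. That is nearly true of the analysis section (COMT also has a column graph), but the abstract and Discussion announce PK-PD modelling and correlation, without a method.
- A reader might take the Discussion's "we plan to use ELISA to measure the activity of COMT" to mean that enzyme amount, not activity, is measured. Both places that describe the COMT assay say activity, and nothing in the documents shows otherwise.
- A reader might extend the point to the primary objective. That objective concerns enzyme activity and does not require exposure ratios for salvianolic acid B.

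The condensed-article defence does not dispose of the rest. The article assigns a method to each outcome and fixes an analysis for the PD index, and that analysis does not answer the objective stated for it. This is a mismatch within the text, not only a missing detail.

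**Conclusion.** The point holds in a limited form. As written, the salvianolate exposure-response part has no named exposure measurement in 12 of 18 patients and no matching analysis. The aspirin part is feasible on 72 scheduled pairs per PD marker from 12 patients, but the analysis section does not use them. The arm comparisons of enzyme activity are not affected.

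This rests on three assumptions: that the article's list of assays is meant to be complete for the outcomes it covers; that all scheduled samples are obtained and the concentrations can be quantified; and that the full protocol or SAP does not already name a salvianolate assay and an exposure-response model. If it does, the remedy is to bring the article's outcome and analysis text into line with it. The matter should be settled before analysis.

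**What to change.** 1. **PD index (analysis section).** Make a within-patient exposure-response analysis the analysis for the secondary objective: for example, a mixed model of each PD marker on concentration at the same draw, with patient as a random effect, over the six shared times. Keep the ANOVA as a supporting comparison of arms.
2. **Primary outcome (measurements).** Add salvianolic acid B concentration by LC-MS/MS on samples already drawn, and compare its exposure between the experimental and salvianolate arms.
3. **If sample volume or stability does not allow step 2,** limit the exposure-response objective and the PK-PD claim in the abstract, Objectives and Discussion to aspirin.

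Cost: one more validated analyte, some analysis work and revised wording. No extra patients or blood draws are scheduled by this change. The article gives no sample volume or stability data, so whether existing samples suffice must be checked first. With 12 patients per drug the model should stay simple, and its estimates should be reported with confidence intervals as exploratory.

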## Methods/design

The trial is conducted in accordance with the ethical principles laid down in the Declaration of Helsinki (as revised in 1983), the Guideline for Good Clinical Practice (China, 2003 and Exposure draft in 2017), and local laws. Written informed consent was obtained from all patients enrolled after a complete and extensive description of the study and before any trial-related procedures were conducted. The trial was approved by the ethics committee of Xiyuan Hospital (Additional file 1).

### Study design

We will conduct a prospectively planned, open-labeled, parallel-grouped, single-centered clinical trial with aggregated PK-PD data (Fig. 1). Eighteen participants will be randomly allocated into three arms: participants in the aspirin arm will be administered with aspirin (100 mg QD) orally; participants in the salvianolate injection arm will be injected with salvianolate (200 mg + 5% glucose injection 250 mL, i.v.); and participants in the experimental arm will be administered with aspirin (100 mg QD) orally and injected with salvianolate (200 mg + 5% glucose injection 250 mL, i.v.). All treatment courses will last for 10 days. Blood samples will be acquired before administration on days 8, 9, and 10, and after administration at 5 min, 15 min, 30 min, 45 min, 1 h, 2 h, 4 h, 8 h, 12 h, and 24 h on day 10 (Fig. 2).

**Fig. 1 Fig1:**
[figure not shown]
ᅟ

**Fig. 2 Fig2:**
[figure not shown]
SPIRIT figure

### Study setting

The trial site will be outpatient care of the Cardiology Department at Xiyuan Hospital in China. Staff at all relevant clinics will be informed about the availability of the trial and they will refer participants to the study investigators. Intravenous therapy will be conducted in the emergency department at Xiyuan Hospital. Participants will be admitted to the hospital on day 9 and will complete the sampling period on days 10 and 11. Clinical biological samples will be sent to a pharmacokinetics laboratory for detection and pharmacokinetic data analysis.

### Study participants

To be included in the trial, participants must: (1) be aged 35–65 years; (2) meet the diagnostic criteria of CHD; (3) meet the diagnostic criteria of stable angina pectoris; (4) meet the diagnostic criteria of blood stasis; (5) meet the diagnostic criteria of grade I–II angina according to the Canadian Cardiovascular Society (CCS); (6) take regular aspirin or salvianolate injection within one month prior; and (7) be informed of the study and voluntarily sign an informed consent.

Exclusion criteria include: (1) severe heart disease (acute myocardial infarction or acute myocardial infarction in six months), severe cardiopulmonary dysfunction (e.g. cardiac function II); (2) poorly controlled hypertension (systolic pressure > 160 mmHg; or diastolic pressure > 100 mmHg); (3) diabetes; (4) severe primary diseases, such as liver and renal hematopoietic system damage, liver function (ALT ≥ 2 × ULN, AST ≥ 2 × ULN), kidney function (Cr > 1.0 × ULN), or nervous and mental disorder; (5) pregnant, breast-feeding, and menstruating women, as well as women planning pregnancy within three months; (6) having participated in clinical trials in the last three months; (7) underwent surgery or had hemorrhagic tendency in the last four weeks; (8) drug allergy history or with allergic constitution; (9) mental or physical disorders; (10) poor compliance or unsuitability for this clinical trial by investigator’s judgment.

Termination criteria include:

Participant terminationSerious adverse events which affect the normal life of participants or obvious abnormal value of the laboratory tests appear in the process of trial, in which case the researchers should decide to terminate the trial and immediately notify the sponsor.The researchers believe that it is necessary to stop the individuals from continuing to participate in the trial because of medical, safety, or regulatory and GCP considerations.

Trial terminationHalf of the participants have mild adverse events.The researchers believe that it is necessary to abort the test for medical, safety, or regulatory purposes and for GCP.

